# 11. Data Analysis and Statistical Considerations

## 11.1 Study Design Considerations

This is a prospective single-arm clinical study to evaluate luspatercept for promoting hematopoietic recovery in patients with poor hematopoietic reconstitution after allo-HSCT. The dose of luspatercept ranged from 0.7 to 1.4 mg/kg subcutaneously on the basis of routine supportive therapy. In patients with symptoms of drug allergies, such as nausea, vomiting, rash, and bronchospasm, or in patients with disease relapse, the drug will be discontinued immediately.

### 11.1.1 Sample Size Assumptions

The number of patients eligible for luspatercept treatment was estimated based on the 20-day hematologic improvement-erythroid (HI-E) reported by Vanstraelen et al.[^1^](#_ENREF_1_1) The present study was planned to detect a 20-day ORR of 28% in patients receiving luspatercept treatment from the reference rate of 14%, controlling for type I and II error rates at 5 and 20%, respectively. Considering an expulsion rate of 10%, a total of 64 patients were planned to be enrolled.

### 11.1.2 Primary Efficacy Endpoint

The primary endpoint was defined as hematologic improvement-erythroid (HI-E), which included the achievement of red blood cell transfusion independence (RBC-TI) for patients requiring RBC transfusions before administration, as well as a mean Hb increase ≥ 1.5 g/dL for RBC-TI patients at the first administration.

### 11.1.3 Secondary Efficacy Endpoints

The secondary endpoints included proportions of patients who achieved absolute increases in neutrophil ≥ 0.5 × 10^9^/L and platelet counts ≥ 30 × 10^9^/L, respectively; proportions of patients who achieved HI-neutrophil (HI-N) and HI-platelet (HI-P) counts; measurements of white blood cell (WBC), absolute neutrophil and platelet counts; and mean changes from baseline.

## 11.2 Data Analysis Considerations

### 11.2.1 Analysis Population

Sixty-four patients with poor hematopoietic reconstitution after allo-HSCT at Peking University People’s Hospital will be enrolled in the luspatercept group.

### 11.2.2 Analysis Plan

### 11.2.2.1 Baseline Data

Baseline characteristics will be summarized and described in a frequency list.

### 11.2.2.2 Analysis of Efficacy

The definitions of the efficacy endpoints have been described in detail in the previous section.

The efficacy endpoints will be hematologic improvement-erythroid, hematologic improvement-leukocyte and hematologic improvement-platelet. GraphPad Prism 10 (GraphPad Software, Inc., La Jolla, CA) will be used for the statistical analyses. The Mann‒Whitney U test will be used for continuous variables, and paired t tests will be performed to analyse the matched or paired data. *P* values <0.05 will be considered to indicate statistical significance.

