| **Statistical analysis** | Statistical analyses will be performed based on the intent-to-treat (ITT) population.  **Primary Efficacy Analysis:**  Primary Outcome Measure:  1. Hematologic improvement-erythroid (HI-E)   1. For patients requiring RBC transfusions before administration: the achievement of red blood cell transfusion independence (RBC-TI) 2. For RBC-TI patients at the first administration: mean Hb increase ≥ 1.5 g/dL   **Secondary Efficacy Analysis:**  1. Hematologic improvement-leukocyte  1) Proportions of patients who achieved absolute increases in neutrophil ≥ 0.5 × 10^9^/L;  2) Proportions of patients who achieved HI-neutrophil (HI-N):  HI-N was defined as a neutrophil count of < 1 × 10^9^/L at pretreatment and the achievement of an absolute neutrophil increase of ≥ 0.5 × 10^9^/L after treatment;  3) Measurements of white blood cell (WBC), absolute neutrophil and mean changes from baseline.  2. Hematologic improvement-platelet  1) Proportions of patients who achieved absolute increases in platelet counts ≥ 30 × 10^9^/L;  2) Proportions of patients who achieved HI-platelet (HI-P):  HI-P was defined as a platelet increase of ≥ 30 × 10^9^/L among patients with pretreatment levels < 100 × 10^9^/L;  3) Measurements of platelet counts and mean changes from baseline.  **Safety Analyses:**  Safety and tolerability will be assessed by the incidence and severity of AEs and changes from baseline of all relevant parameters, including laboratory test values, physical examination findings, vital signs, and ECOG performance scores. With the exception of haematologic AEs, all AEs will be graded according to the National Cancer Institute Common Toxicity Criteria version 5.0. All subjects will be monitored for AEs within 20 days post-treatment. |
|  |  |

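### No test named in the efficacy section fits the hypothesis the trial is sized on (HI-E 28% against a fixed 14%), which leaves the pass mark at 15 or 16 of 64

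*Protocol*

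**What the plan says.** Section 11.1 describes the design: "This is a prospective single-arm clinical study to evaluate luspatercept for promoting hematopoietic recovery in patients with poor hematopoietic reconstitution after allo-HSCT". Section 11.1.1, repeated in the Study Synopsis, sets the hypothesis. The trial was "planned to detect a 20-day ORR of 28% in patients receiving luspatercept treatment from the reference rate of 14"%. The error rates given there are 5% for type I and 20% for type II. The same section then adds: "Considering an expulsion rate of 10%, a total of 64 patients were planned to be enrolled".

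Sections 6.2 and 11.1.2 define the primary endpoint, HI-E, by response criteria: transfusion independence for patients transfused before treatment, or a haemoglobin rise of at least 1.5 g/dL for the others. Sizing on a response rate makes this a yes/no outcome per patient. The Synopsis gives the denominator: "Statistical analyses will be performed based on the intent-to-treat (ITT) population".

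Section 11.2.2.2 lists HI-E first among the efficacy endpoints. Its methods are the Mann-Whitney "U test will be used for continuous variables, and paired t tests will be performed to analyse the matched or paired data", and P "values <0.05 will be considered to indicate statistical significance".

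The protocol nowhere gives a test or interval for a proportion, an analysis against 14%, a side for the 5% level, or a responder cut-off. Its one sentence on summarising categorical data is in the safety section (11.2.2.3) and is descriptive.

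**The concern.** Two sections of the same document do not meet. Section 11.1.1 poses a question about one proportion and a fixed reference. Section 11.2.2.2 supplies tools for other questions. Mann-Whitney compares two independent samples of a continuous or ordinal variable, and this trial has one arm with no subgroup comparison defined. If it were applied to before/after counts, it would ignore the pairing. The paired t test asks whether a mean change differs from zero and says nothing about 14%.

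Two things are at stake. First, the choice of primary test decides whether a borderline count of responders is a success. The study is open-label (section 5.2), so a choice left until analysis could be made with the results in view. Second, the only P values the section provides for would come from changes from baseline in patients enrolled because their counts were poor, treated alongside routine supportive care and without a control arm. Such P values could reflect spontaneous recovery, and could be read as the efficacy result although they do not address the planned hypothesis.

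**Working it through.** **Inputs.** p0 = 0.14, p1 = 0.28, type I error 5%, type II error 20%, 10% loss, N = 64 (section 11.1.1); one arm (11.1); ITT denominator (Synopsis), taken as all 64 enrolled. The side of the 5% level is not stated.

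**Step 1: reproduce 64.** One-sample normal approximation:

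n = [(z_α·√(p0(1−p0)) + z_β·√(p1(1−p1))) / (p1−p0)]²

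with √(0.14×0.86) = 0.3470, √(0.28×0.72) = 0.4490 and z_β = 0.8416.

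- Two-sided 5% (z_α = 1.960): [(0.6801 + 0.3779)/0.14]² = 57.1; 57.1/0.9 = 63.5, rounded up to **64**.
- One-sided 5% (z_α = 1.645): 45.9; 45.9/0.9 = 51.01, rounded up to 52.

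Other one-sample methods, after the 10% allowance, also miss 64: one-sided exact binomial 51 → 57; exact with 2.5% per tail 67 → 75; arcsine 57 (one-sided) or 73 (two-sided). The stated size therefore points to a two-sided 5% one-sample test of a proportion, which section 11.2.2.2 does not name.

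**Step 2: smallest number of responders out of 64 that rejects 14% at 0.05.**

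| Test | Pass mark | P at the mark | P one below |
|---|---|---|---|
| Two-sided score (z) | 15 | 0.030 | 0.069 |
| Two-sided exact, likelihood-ordered | 15 | 0.045 | 0.073 |
| Two-sided exact, doubled tail | 16 | 0.027 | 0.058 |
| Two-sided Wald | 16 | 0.042 | 0.075 |
| One-sided exact | 15 | 0.029 | 0.057 |
| One-sided score (z), uncorrected | 14 | 0.035 | 0.073 |

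Example, score test at 15: (0.2344 − 0.14)/√(0.1204/64) = 0.0944/0.0434 = 2.18, two-sided P = 0.030.

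The 95% Clopper-Pearson lower limit is 13.75% at 15/64 (below 14%) and 15.0% at 16/64 (above it). The Wilson lower limit at 15/64 is 14.75%.

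**Step 3: exact properties of each mark, X ~ Binomial(64, p).**

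| Mark | Observed rate | P(X ≥ mark) at 14% | Power at 28% |
|---|---|---|---|
| 14 | 21.9% | 5.7% | 89.3% |
| 15 | 23.4% | 2.9% | 82.9% |
| 16 | 25.0% | 1.35% | 74.6% |

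A mark of 14 exceeds 5%. A mark of 16 misses the planned 80% power. A mark of 15 meets both stated error rates: as a likelihood-ordered two-sided test its P is 0.045, and its power is 82.9%.

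**Step 4: how often 15 versus 16 decides the result.** Only when exactly 15 respond: 2.89% − 1.35% = 1.5% of trials at a true 14%, and 82.9% − 74.6% = 8.3% at a true 28%.

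**Sensitivity to N.** If only 57 patients were in the denominator, the two-sided score test, both exact versions and the Clopper-Pearson limit would all give 14, and Wald would give 15. The mark has to be recomputed if N differs.

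**The case against.** The strongest reply is that this is an omission a statistical analysis plan could fill. Section 11.2.2.2 ties its tests to continuous and paired data, and the protocol has such endpoints: white cell, neutrophil and platelet values and their changes from baseline. It does not assign either test to HI-E. The reference rate, the target and the error rates are all stated, so the hypothesis is fixed and only its test is unnamed.

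Much of this stands. A reader might infer that the protocol gives the primary endpoint a wrong test, or that the trial can never test its question; the text supports neither. The reply does not remove the mismatch. The protocol does not defer the choice. It gives its own efficacy tests and significance rule, and these do not reach the hypothesis in section 11.1.1.

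A second reply is that the ambiguity is small. Sample size reproduction makes a two-sided reading the natural one, and only a count of exactly 15 is then in dispute. That is correct. A reader might place 14 on the same footing because no side is stated. But 14 arises only from an uncorrected one-sided 5% z test, which does not reproduce 64 and has an exact type I error of 5.7%.

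Third, one arm does not rule out Mann-Whitney altogether. Patients transfused at baseline and those who were not could be compared. The protocol plans no such comparison, so it is fair to ask what the test is for.

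**Conclusion.** The concern holds in this form: the efficacy section names no test that fits the hypothesis the trial is sized on, and it names one test for which no second group is defined. The sample size itself is not in error. With all 64 in the ITT denominator and a two-sided 5% level (inferred from N, not stated), the pass mark is 15 or 16 depending on the test. The corresponding powers are 82.9% and 74.6%, and the upper-tail errors 2.9% and 1.35%. The numerical gap is narrow, but it bears on the primary conclusion.

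A reader might also infer that spontaneous recovery alone would make the before/after tests significant. The documents give no recovery rate, no variability of counts and no baseline count threshold for entry, so it can be said only that those P values could reflect it.

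**What to change.** In section 11.2.2.2, name the primary analysis: a one-sample binomial test of the HI-E proportion against 14% in the ITT set, with a 95% confidence interval. Fix the version of the test, its side and the responder cut-off before analysis. Two choices are consistent at N = 64:

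- **At least 15 responders**, by a likelihood-ordered two-sided exact test (P = 0.045 at 15, power 82.9%). This meets both stated error rates. The interval should agree with the test: Wilson does at 15/64, whereas Clopper-Pearson would include 14%.
- **At least 16 responders**, by 2.5% per tail with the Clopper-Pearson interval. Section 11.1.1 and the Synopsis should then restate power as about 75%.

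Add that the mark is recomputed if N differs. For changes from baseline in blood counts, replace Mann-Whitney with a paired method, or state which two groups it compares. Label the P values from changes from baseline descriptive.

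The cost is protocol wording; the second choice also carries a lower stated power. No change to N or data collection is needed for either choice.

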### 11.2.2.3 Analysis of Safety

Safety and tolerability will be assessed by the incidence and severity of AEs and changes from baseline of all relevant parameters, including laboratory test values, physical examination findings, vital signs, and ECOG performance scores. The definition of AEs has been detailed in previous section. With the exception of haematologic AEs, all AEs will be graded according to the National Cancer Institute Common Toxicity Criteria version 5.0. All subjects will be monitored for AEs within 20 days post-treatment. Categorical data will be summarized by the proportion of total subjects. Quantitative data will be described using arithmetic averages or medians for central tendencies and standard deviations or interquartile ranges for distribution ranges.

# 12. Materials for the Study

All materials that will be provided to the study sites and investigators are as follows:

- The study protocol
- Informed consent
- CRF

# 13. Ethical Considerations

## 13.1 Responsibility of Investigators

The investigators are responsible for guaranteeing the compliance of the clinical study with the protocol, the Chinese good clinical practice (GCP) guidelines and applicable laws and regulations.

## 13.2 Informed Consent Process

Prior to participation in the study, the subjects must be informed about the objectives, methods, possible benefits, potential risks and possible discomforts of the study by the investigators. They also should be informed that participation in the study would be voluntary, that they can withdraw from the study at any time, that there is no impact on the treatment of the disease whether they take part in the study, and that their privacy will be protected.

Subjects or their legally acceptable representatives should have enough time to read the informed consent form and raise queries. Written informed consent must be obtained from each subject or their legally acceptable representative.

## 13.3 Good Clinical Practice

This study will be conducted in accordance with the Declaration of Helsinki and the Chinese GCP. The study will be conducted only if it is approved by the ethical review committee of the principal study site. The investigators will guarantee that the study will be conducted in accordance with applicable laws and regulations and the scientific and ethical principles of the People’s Republic of China. If the protocol needs revision during the study, the revised version must be reapproved by the ethical review committee of the principal study site. If new data related to study treatment are discovered, the informed consent must be revised, and the revision must be reapproved by the ethical review committee of the principal study site and subjects.

## 13.4 Protection of Subjects’ Personal Data

The data collected in the study are limited in terms of efficacy and safety related to the study treatment. Data will be collected and used in accordance with applicable laws and regulations.

# 14. Administrative Requirements

Neither the investigator nor the applicant can revise the protocol without agreeing on the opposite side. All revisions of the protocol must be released by the applicant institution. To ensure the integrity, accuracy and reliability of the data, the relevant examination and treatment results must be documented in the original medical records and the CRF. Independent clinical monitoring will be performed regularly by a panel of qualified and experienced study investigators composed of haematologists who are blinded to the treatment assignments.

# 16 Appendices

## 16.1 Appendix 1

**ECOG Performance Status**

| **Grade** | **ECOG** |
| --- | --- |
| **0** | Fully active, able to carry on all predisease performance without restriction |
| **1** | Restricted in physically strenuous activities but ambulatory and able to carry out work of a light or sedentary nature, e.g., light house work or office work |
| **2** | Ambulatory and capable of all selfcare but unable to carry out any work activities; up and about more than 50% of waking hours |
| **3** | Capable of only limited selfcare; confined to bed or chair more than 50% of waking hours |
| **4** | Completely disabled; cannot carry out any selfcare; totally confined to bed or chair |
| **5** | Dead |

